**19b. Presentation of adherence data.**

If gross inability to follow allocated study group is detected, data will be presented in publication reporting on the primary outcome.

It is expected that some patients will forget to administer one-several doses of their LPS during the trial, seeing as the medication is administered three times daily. While all deviations will be accounted for by the participating study clinics, minor deviations in adherence to study interventions will not be publicly reported.

**19c. Definition of protocol deviations.**

All deviations from protocol will be reported and registered in the online case report form (CRF)/study database. Minor deviations may include, but is not limited to missingness of blood samples, study visits planned at day not suggested in protocol and errors during randomisation.

Major protocol deviations (patient or clinic not being able to comply with allocated study group) will be reported to the primary investigator (PI) continuously via the CRF.

**19d. Summary and presentation of protocol deviations.**

AP (PI), KL and MS will assess protocol deviations continuously during the trial. Minor protocol deviations will not be publicly presented. Major protocol deviations will be reported in the primary outcome paper.

## 20. Analysis Populations

Per-transfer (primary population): Women randomised, undergoing embryo transfer

Intention-to-treat: Women randomised.

As-treated: Women randomised, grouped according to treatment received.

Per-protocol: Women randomised, undergoing allocated treatment.

Women withdrawing consent to participate in the trial will be removed from all analyses.

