## Withdrawal/Follow-Up

### 24a-c. Levels and reasons for withdrawal or loss to follow-up.

“A patient can withdraw from the study at any time. Further, participation in the study can be interrupted by the non-treating and the treating doctors, if one of the following criteria is present:

- The patients general condition contraindicates participation
- Protocol violation, which the investigator considers having influence on the treatment”[1]

We do not expect patients to be lost to follow-up during the fertility treatment course or during pregnancy. Home-birth is not common in Denmark, still, information regarding potential obstetric complications and perinatal outcomes might be lost should a patient decide to give birth without involvement of the public health sector.

In the case of missing outcome data, this will be publicly disseminated in the primary outcome paper.

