## Section 6: Analysis

### Outcome Definitions

#### 26a-b. Specification, unit, measurement method and timing of primary and secondary outcomes

| Out-come                  | Definition                                                                     | Unit   | Method of measurement                                 | Time of evaluation                                                                                                                                       |
|---------------------------|--------------------------------------------------------------------------------|--------|-------------------------------------------------------|----------------------------------------------------------------------------------------------------------------------------------------------------------|
| Primary outcome    |                                                                                |        |                                                       |                                                                                                                                                          |
| Live birth                | Defined as live birth following GA 22+0 weeks.                                 | Yes/no | Registration in medical records                       | Approximately one year after inclusion in trial (one-year follow-up) for all patients with a verified clinical pregnancy and no record of pregnancy loss |
| Secondary outcomes |                                                                                |        |                                                       |                                                                                                                                                          |
| Clinical pregnancy        | Intrauterine embryo with fetal heartbeat detected at the early pregnancy scan. | Yes/no | Vaginal ultrasound                                    | Assessed at the early pregnancy scan planned in gestational week 8 of all patients with a positive pregnancy test                                        |
| Pregnancy                 | s-hCG $\geq$ 5 IU/L                                                            | Yes/no | Blood sample                                          | 16 days following ovulation trigger                                                                                                                      |

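### The intention-to-treat set drops women who withdraw consent, so after any withdrawal no analysis set holds all randomised women, and the comparisons can be biased if withdrawal is related to allocation and live birth

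*SAP*

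**What the plan says.** SAP section 20 defines four analysis sets:

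- "Per-transfer (primary population): Women randomised, undergoing embryo transfer"
- "Intention-to-treat: Women randomised"
- "As-treated: Women randomised, grouped according to treatment received"
- "Per-protocol: Women randomised, undergoing allocated treatment"

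The section closes with a rule that applies to all four: "Women withdrawing consent to participate in the trial will be removed from all analyses".

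Sections 24a-c add "A patient can withdraw from the study at any time" and "We do not expect patients to be lost to follow-up during the fertility treatment course or during pregnancy". They give no expected number of consent withdrawals. They also do not separate stopping trial participation from refusing further use of data. For live birth, section 26a-b gives the method of measurement as "Registration in medical records". Section 27e plans no sensitivity analysis. Section 28, on missing data, covers only how rates are displayed.

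**The concern.** The per-transfer and per-protocol sets are subsets of the randomised women by definition. ITT and as-treated are the only two sets defined on everyone randomised, and the closing sentence cuts both. The ITT label then no longer matches the SAP's own definition.

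This matters because the primary set is formed after randomisation. Women are randomised on the day of the hCG trigger (section 10) and enter the primary set only if they reach embryo transfer. ITT is the one analysis by allocated group that is meant to be free of such selection.

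Withdrawal could plausibly depend on arm and on outcome. The trial is single-blinded (section 9). Comparison I sets vaginal progesterone, taken three times daily (section 19b), against none, and the SAP describes no placebo. The removal rule has no time limit, so a woman may withdraw after a negative test at trigger + 16 days (section 15) or after a loss. She then leaves both numerator and denominator, and the planned n/N display does not show that she was there.

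**Working it through.** **Inputs.** From section 11: 604 women, live birth 21% against 31%, 80% power, 5% level. From section 9: allocation 1:1:1:1, so each marginal comparison has 604/2 = 302 women per arm. The withdrawal share and the live birth rate among women who withdraw are not in the SAP and are assumed below.

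**The plan's own figure.** Two-sided test, pooled variance, no continuity correction:

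n per arm = [1.960·√(2·0.26·0.74) + 0.842·√(0.21·0.79 + 0.31·0.69)]² / 0.10² = 301 (rounded up), or 602 in total. This agrees with 604 to within rounding. Power at 302 per arm is 80.2%. The sample size is not in dispute.

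**Effect of deletion.** Let p be the arm's true live birth rate, w the share withdrawing and q the live birth rate among those who withdraw. After deletion the expected rate is

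(p − w·q) / (1 − w).

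Take no true effect, p = 21% in both arms, and withdrawal in one arm only. The spurious difference is the expression above minus p. Type I error is the two-sided normal approximation with pooled standard error, 302(1 − w) against 302 women, nominal 5%.

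| w | q | Rate after deletion | Spurious difference | Type I error |
|---|---|---|---|---|
| 2% | 0 | 0.21/0.98 = 21.43% | +0.43 points | 5.19% |
| 5% | 0 | 0.21/0.95 = 22.11% | +1.11 points | 6.23% |
| 10% | 0 | 0.21/0.90 = 23.33% | +2.33 points | 10.32% |
| 2% | 10.5% | (0.21 − 0.0021)/0.98 = 21.21% | +0.21 points | 5.05% |
| 5% | 10.5% | (0.21 − 0.00525)/0.95 = 21.55% | +0.55 points | 5.31% |
| 10% | 10.5% | (0.21 − 0.0105)/0.90 = 22.17% | +1.17 points | 6.33% |
| any | 21% | 21% | 0 | 5% |

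In counts: 63 live births among 302 women is 20.9%. Deleting 10 women without a live birth gives 63/292 = 21.6%, and deleting 20 gives 63/282 = 22.3%.

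**When withdrawal is balanced.** If it is unrelated to outcome and equal in both arms, only power is lost: from 80.2% to 79.4%, 78.1% and 75.9% at 2%, 5% and 10%. If equal shares withdraw in both arms and none of them has a live birth, no false difference arises where there is none. A true 10-point difference is scaled by 1/(1 − w), for example 10/0.95 = 10.5 points at 5%.

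**The case against.** Four points can be made for the plan.

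*The rule covers withdrawn consent only.* This stands. A reader might infer that women who stop progesterone or miss their allocated day are also deleted. The SAP does not say that. Women transferred on another day stay in the per-transfer, ITT and as-treated analyses (section 19a), and missed doses are treated as minor deviations (section 19b).

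*Live birth in medical records may be out of reach after withdrawal.* This stands in part. That the outcome sits in a record does not show that the trial may use it once consent is withdrawn. The answer depends on consent text that is not at hand. The Danish restrictions in sections 21 and 23 concern women who never consented, so they settle the matter neither way.

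*The primary analysis is less exposed.* This also stands. The objective is live birth per transfer (section 8), and a woman who leaves before transfer is outside that set whatever the rule says. For the primary set, the rule matters for withdrawals after transfer.

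*Reporting is already planned.* A CONSORT diagram (section 23), disclosure of missing outcome data (sections 24a-c) and rates as n/N (section 28) may reveal the losses. They do not return any woman to an analysis, so this does not answer the point.

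**Conclusion.** The contradiction within section 20 is plain and needs no assumption: ITT is defined as all randomised women, and the next rule removes some of them. Once any woman withdraws consent, no set contains everyone randomised.

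The consequence for the estimates is conditional. A reader might infer that unequal withdrawal by itself biases every analysis. It does not: with no relation between withdrawal and live birth the bias is zero, however unequal the withdrawal. Under the assumptions above the spurious difference is about 0.2 to 2.3 points against a 10-point target. At 2% to 5% withdrawal the type I error rises at most to 6.2%, and it reaches 10.3% only at 10% one-arm withdrawal with no live births among those women. The direction favours the arm with more withdrawals when those women do worse than the rest of their arm, and reverses when they do better.

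The SAP gives no withdrawal rate, so nothing shows that the larger figures will arise. The point should be fixed, because the ITT label would otherwise be inaccurate and the repair is cheap. The documents do not support treating it as a critical flaw.

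**What to change.** Replace the closing sentence of section 20 with a rule to this effect:

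- Women who withdraw from further participation remain in the ITT population in their allocated group. Data collected up to withdrawal, and live birth from medical records, are used where their consent permits.
- Only women who refuse use of their data have outcomes set to missing. They are counted by allocated group, with timing relative to transfer where this may be recorded.

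In section 27e, add a sensitivity analysis of the ITT result on all randomised women. Count missing outcomes first as no live birth, then as best and worst case by arm. With x live births and m missing outcomes among n women in each arm (1 and 0), the extremes are (x₁ + m₁)/n₁ − x₀/n₀ and x₁/n₁ − (x₀ + m₀)/n₀. Their width is m₁/n₁ + m₀/n₀, so 5% missing in one arm alone gives bounds 5 points wide. They are limits, not estimates. For the per-transfer analysis, apply the same bounds only to women who withdrew after transfer.

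The bounds need only counts by arm for the women whose data may not be used. The cost is revised wording, a check of the consent text on use of data after withdrawal, and one short extra analysis. The change should be made before outcomes are compared by group.

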# Section 5: Trial Population

## 21. Screening Data

Screening data will not be reported due to Danish legislation not allowing for collection of data on women not consenting to trial participation.

## 22. Eligibility

“Women fulfilling following criteria:

- Age 18-41 years
- Regular menstrual cycle (23-35 days)
- Planned to undergo single blastocyst transfer in a modified natural cycle with a high-quality (Gardner 3-6 A/B), vitrified blastocysts derived from 1.-3. IVF/ICSI cycle resulting in an embryo transfer on a public hospital.
- Giving informed consent

Exclusion criteria:

- Previous participation in the study
- Uterine malformations, intrauterine polyps or submucosal myomas
- Current breast feeding
- Receiving oocyte donation
- Preimplantation genetic testing for heritable diseases
- Blastocyst conceived with sperm from testicular sperm aspiration
- Active HIV or hepatitis B and C infection
- Known luteal phase insufficiency

Further exclusion criteria are the following contraindications to progesterone: allergy to the study medication, undiagnosed vaginal bleeding, current missed abortion or ectopic pregnancy, hepatic insufficiency or severe hepatic disease, history of genital or breast cancer, history of arterial or venous thromboembolism, thrombophlebitis or porphyria.”[1]

## 23. Recruitment

Patients scheduled to start FET treatment in a mNC will be recruited continuously through oral and written communication.

A standard CONSORT diagram will be made with exception of the number of women screened for participation.[3] Danish GDPR legislation does not allow for collection of data on women not giving consent to participate in the trial.

## Withdrawal/Follow-Up

### 24a-c. Levels and reasons for withdrawal or loss to follow-up.

“A patient can withdraw from the study at any time. Further, participation in the study can be interrupted by the non-treating and the treating doctors, if one of the following criteria is present:

- The patients general condition contraindicates participation
- Protocol violation, which the investigator considers having influence on the treatment”[1]

We do not expect patients to be lost to follow-up during the fertility treatment course or during pregnancy. Home-birth is not common in Denmark, still, information regarding potential obstetric complications and perinatal outcomes might be lost should a patient decide to give birth without involvement of the public health sector.

In the case of missing outcome data, this will be publicly disseminated in the primary outcome paper.

## 25. Baseline Patient Characteristics

### 25a-b. List of baseline characteristics to be summarized and methods for summarizing baseline characteristics

| Baseline characteristics to be summarized | Unit                                                     | Method for summarizing baseline characteristics          |
|-------------------------------------------|----------------------------------------------------------|----------------------------------------------------------|
| Age                                       | Years                                                    | Means (SD) or median (IQR) depending on the distribution |
| Age ≥37 years                             | Years                                                    | n (%)                                                    |
| Age ≥35 years                             | Years                                                    | n (%)                                                    |
| Ethnicity                                 | Caucasian, African, Afro-Caribbean, Asian, Inuit, other. | n (%)                                                    |
| Civil status                              | Heterosexual, homosexual or single.                      | n (%)                                                    |

|                           |                                                                                                     |                                                          |
|---------------------------|-----------------------------------------------------------------------------------------------------|----------------------------------------------------------|
| Body mass index           | Kg/m                                                                                    | Means (SD) or median (IQR) depending on the distribution |
| Smoking daily             | Yes/no                                                                                              | n (%)                                                    |
| Menstrual cycle length    | Days                                                                                                | Means (SD) or median (IQR) depending on the distribution |
| Duration of infertility   | Years                                                                                               | Means (SD) or median (IQR) depending on the distribution |
| Antral follicle count     | N                                                                                                   | Means (SD) or median (IQR) depending on the distribution |
| AMH                       | pmol/L                                                                                              | Means (SD) or median (IQR) depending on the distribution |
| Cause of infertility      | Anovulation, tubal factor, cervical uterine factor, endometriosis, male factor, unexplained, other. | n (%)                                                    |
| Number of IVF/ICSI cycles | 1, 2, 3                                                                                             | n (%)                                                    |
| Number of FET cycles      | 1, 2, ≥3                                                                                            | n (%)                                                    |
| Previous childbirth       | Yes/no                                                                                              | n (%)                                                    |
| Previous pregnancy        | Yes/no                                                                                              | n (%)                                                    |

SD = standard deviation, IQR = interquartile range, AMH = anti-Müllerian hormone, IVF = in vitro fertilisation, ICSI = intracytoplasmic sperm injection, FET = frozen embryo transfer

| Treatment characteristics to be summarized | Unit and | Method for summarizing baseline characteristics   |
|---------------------------------------------------|-----------------|----------------------------------------------------------|
| Cycle day of ovulation trigger                    | Cycle day       | Means (SD) or median (IQR) depending on the distribution |
| Size of leading follicle at trigger               | mm              | Means (SD) or median (IQR) depending on the distribution |
| Endometrial thickness at trigger                  | mm              | Means (SD) or median (IQR) depending on the distribution |

|                                                                       |                                            |       |
|-----------------------------------------------------------------------|--------------------------------------------|-------|
| Method of fertilisation of blastocyst rated best at time of inclusion | IVF/ICSI                                   | n (%) |
| Blastocyst Gardner score                                              | 3AA/AB/BA/BB, 4AA/AB/BA/BB, 5-6AA/AB/BA/BB | n (%) |
| Day of blastocyst vitrification                                       | Day 5/ day 6                               | n (%) |

SD = standard deviation, IQR = interquartile range, IVF = in vitro fertilisation, ICSI = intracytoplasmic sperm injection

## Section 6: Analysis

### Outcome Definitions

#### 26a-b. Specification, unit, measurement method and timing of primary and secondary outcomes

| Out-come                  | Definition                                                                     | Unit   | Method of measurement                                 | Time of evaluation                                                                                                                                       |
|---------------------------|--------------------------------------------------------------------------------|--------|-------------------------------------------------------|----------------------------------------------------------------------------------------------------------------------------------------------------------|
| Primary outcome    |                                                                                |        |                                                       |                                                                                                                                                          |
| Live birth                | Defined as live birth following GA 22+0 weeks.                                 | Yes/no | Registration in medical records                       | Approximately one year after inclusion in trial (one-year follow-up) for all patients with a verified clinical pregnancy and no record of pregnancy loss |
| Secondary outcomes |                                                                                |        |                                                       |                                                                                                                                                          |
| Clinical pregnancy        | Intrauterine embryo with fetal heartbeat detected at the early pregnancy scan. | Yes/no | Vaginal ultrasound                                    | Assessed at the early pregnancy scan planned in gestational week 8 of all patients with a positive pregnancy test                                        |
| Pregnancy                 | s-hCG $\geq$ 5 IU/L                                                            | Yes/no | Blood sample                                          | 16 days following ovulation trigger                                                                                                                      |
| Pregnancy loss            | All cases of pregnancy loss follow-                                            | Yes/no | Registration in medical records or detection of empty | Assessed continuously in patients with a positive pregnancy                                                                                              |

|                                     |                                                                                                  |        |                                                                                                              |                                                                                                                                                          |
|-------------------------------------|--------------------------------------------------------------------------------------------------|--------|--------------------------------------------------------------------------------------------------------------|----------------------------------------------------------------------------------------------------------------------------------------------------------|
|                                     | ing a positive pregnancy test, before GA 22+0                                                    |        | uterus/fetal demise at early pregnancy scan                                                                  | test, depending on the time point of pregnancy loss                                                                                                      |
| Ectopic pregnancy                   | Pregnancy detected outside of the uterus, using either a) ultrasound or b) histologic testing    | Yes/no | Registration in medical records or detection of ectopic pregnancy during the early pregnancy ultrasound scan | Assessed continuously in all patients with a positive pregnancy test                                                                                     |
| Induced abortion                    | Medically or surgically induced abortion, typically due to congenital abnormality in fetus/child | Yes/no | Registration in medical records                                                                              | Assessed continuously in all patients with a positive pregnancy test                                                                                     |
| Early miscarriage                   | Pregnancy loss before vitrification of a clinical pregnancy                                      | Yes/no | Registration in medical records                                                                              | Assessed continuously in all patients with a positive pregnancy test                                                                                     |
| Late miscarriage                    | Pregnancy loss before vitrification of a clinical pregnancy, before GA 22+0                      | Yes/no | Registration in medical records                                                                              | Assessed continuously in all patients with a positive pregnancy test                                                                                     |
| Obstetric complications      |                                                                                                  |        |                                                                                                              | Approximately one year after inclusion in trial (one-year follow-up) for all patients with a verified clinical pregnancy and no record of pregnancy loss |
| Hypertensive disorders of pregnancy | Including pre-eclampsia, eclampsia and gestational hypertension                                  | Yes/no | Registration in medical records                                                                              |                                                                                                                                                          |

|                                   |                                                                      |        |                                 |                                                                                                                                                          |
|-----------------------------------|----------------------------------------------------------------------|--------|---------------------------------|----------------------------------------------------------------------------------------------------------------------------------------------------------|
| Gesta-
tional
diabe-
tes | Diabetes detected during pregnancy with oral glucose tolerance test. | Yes/no | Registration in medical records |                                                                                                                                                          |
| Post-
partum
bleed-
ing  | Bleeding exceeding 1000 mL                                           | Yes/no | Registration in medical records |                                                                                                                                                          |
| Caesar-
ean sec-
tion       |                                                                      | Yes/no | Registration in medical records |                                                                                                                                                          |
| Perinatal complications    |                                                                      |        |                                 | Approximately one year after inclusion in trial (one-year follow-up) for all patients with a verified clinical pregnancy and no record of pregnancy loss |
| Preterm birth                     | Birth before GA 37+0                                                 | Yes/no | Registration in medical records |                                                                                                                                                          |
| Birth-
weight                  |                                                                      | Grams  | Registration in medical records |                                                                                                                                                          |
| Low birth weight                  | Birthweight < 2500 grams                                             | Yes/no | Registration in medical records |                                                                                                                                                          |
| Very low birth weight             | Birthweight < 1500 grams                                             | Yes/no | Registration in medical records |                                                                                                                                                          |
| Hight birth weight                | Birthweight > 4000 grams                                             | Yes/no | Registration in medical records |                                                                                                                                                          |
| Very high birth weight            | Birthweight > 4500 grams                                             | Yes/no | Registration in medical records |                                                                                                                                                          |

|                           |                                                                                                |        |                                                      |  |
|---------------------------|------------------------------------------------------------------------------------------------|--------|------------------------------------------------------|--|
| Small for gestational age | More than two standard deviation units below expected birth weight.                            | Yes/no | Calculated following collection of birth-weight data |  |
| Large for gestational age | More than two standard deviation units above expected birth weight.                            | Yes/no | Calculated following collection of birth-weight data |  |
| Congenital malformation   | Any congenital malformation                                                                    | Yes/no | Registration in medical records                      |  |
| Perinatal death           | Stillbirth or live birth followed by death within the first week following birth, from GA 22+0 | Yes/no | Registration in medical records                      |  |

GA = gestational age, hCG = human chorionic gonadotropin

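### The late-miscarriage row repeats the early-miscarriage condition, so as written it counts the early losses and leaves out the late ones

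*SAP*

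**What the plan says.** The outcome table in SAP section 26a-b splits miscarriage into two yes/no secondary outcomes in adjacent rows.

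- Early miscarriage: "Pregnancy loss before vitrification of a clinical pregnancy".
- Late miscarriage: "Pregnancy loss before vitrification of a clinical pregnancy, before GA 22+0".

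The dividing event is clinical pregnancy, defined in the same table as "Intrauterine embryo with fetal heartbeat detected at the early pregnancy scan". Its timing is given as "Assessed at the early pregnancy scan planned in gestational week 8 of all patients with a positive pregnancy test".

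The table also has a row for overall pregnancy loss, which takes in all losses after a positive test and before GA 22+0, and separate rows for ectopic pregnancy and induced abortion. Section 26c then computes a rate for each outcome in the table as events over individuals in the study group. No other part of the SAP defines early or late miscarriage, and the version log lists no change to item 26.

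**The concern.** Two categories named early and late should lie on opposite sides of a dividing event. Here both lie on the same side, before it. The only difference is an upper limit of GA 22+0, and losses before a week 8 scan meet that limit anyway.

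The term used for the dividing event is also wrong. Elsewhere the SAP uses vitrification for freezing the blastocyst, as in the characteristic "Day of blastocyst vitrification", and for pregnancies it speaks of a "verified clinical pregnancy and no record of pregnancy loss". Verification is evidently meant.

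At stake is the late-miscarriage rate in both comparisons (progesterone versus none, and transfer on day 6 versus day 7). Anyone who codes the variable from the text obtains the wrong events. Anyone who silently corrects it departs from the written plan without a record.

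**Working it through.** The SAP gives no figure to reproduce here, so the check compares the definitions as sets.

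**Inputs, all from the 26a-b table.** Let V be verification of a clinical pregnancy at the early scan, planned in gestational week 8. Read vitrification as verification in both rows, which is the reading most favourable to the SAP.

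- Early as written = losses before V.
- Late as written = losses before V and before GA 22+0.
- Overall pregnancy loss = losses after a positive test and before GA 22+0.

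**Step 1: relation between the two rows.** Late as written is early as written with one more condition, so every late event is also an early event. Because V is planned for week 8 and the limit is GA 22+0, the added condition removes nothing in practice. The two rows then describe the same set of losses.

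**Step 2: classify each kind of loss.**

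| Loss | Early | Late | Overall loss |
|---|---|---|---|
| After a positive test, before V | yes | yes | yes |
| After V, before GA 22+0 | no | no | yes |

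The unclassified interval runs from about week 8 to week 22, or roughly 22 − 8 = 14 weeks.

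**Step 3: does correcting the word suffice?** No. The table above already assumes that correction. The fault that remains is the word *before* in the late row.

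**Step 4: change *before* to *after* in the late row.** A loss before V is then early only, and a loss from V to GA 22+0 is late only. The overlap and the gap both disappear.

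**Step 5: what else depends on these rows?** Live birth, clinical pregnancy and overall pregnancy loss each have their own definition in the table, and none refers to early or late miscarriage. The sample size in section 11 rests on live birth alone. Sections 14 and 15 list the pregnancy loss rate and do not name the early and late split.

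**The case against.** The strongest reply is that this is an obvious slip and nobody would act on it literally. The row labels, the week 8 dividing event and the otherwise redundant GA 22+0 limit all point to *after verification* as the intended meaning. If context may correct vitrification, it may correct *before* as well. An analyst is unlikely to count every early loss as late and to discard every loss after a heartbeat.

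Much of this stands. The intent is easy to infer, and the error is probably one of drafting. It lowers the seriousness of the point but does not remove it: this table is where the SAP fixes its outcomes, section 26c computes rates from it, and nothing else in the document supplies the right definition.

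Three stronger readings are tempting and are not supported.

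- A reader might infer that both miscarriage outcomes are unusable. Once verification is read, the early row is coherent; the logical error is in the late row.
- A reader might infer that the fault shows because early plus late cannot equal total pregnancy loss. The SAP never says that they should. Ectopic pregnancy and induced abortion have their own rows, so the two miscarriage categories need not sum to overall loss even when correctly defined.
- A reader might infer that the timing of loss is a central question of the trial. Both objectives in section 8 concern live birth per transfer, and the SAP attaches no power calculation or testing hierarchy to the early and late split.

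**Conclusion.** The late-miscarriage definition is wrong as written. Followed literally, it counts the losses it should exclude and excludes the losses it should count. The conclusion rests on two assumptions: that vitrification stands for verification, and that verification takes place at or near the planned week 8 scan. Without the first, neither row has a usable meaning, so the wording needs correction either way.

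The size of the error in the reported rates cannot be given, because the SAP contains no expected number of losses before or after verification. The reach of the error is clear: it affects the division of pregnancy loss into early and late, and nothing else. This is a definition error that should be corrected before analysis. It does not threaten the primary result or the overall pregnancy loss result.

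**What to change.** Amend the table in section 26a-b as follows.

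1. Replace *vitrification* with *verification* in both miscarriage rows.
2. Reword the late row to: *Pregnancy loss after verification of a clinical pregnancy and before GA 22+0*.
3. State that early and late miscarriage are mutually exclusive.
4. State how they relate to the ectopic pregnancy and induced abortion rows. Otherwise an ectopic pregnancy could still be read as a loss before verification, and an induced abortion as a loss after it. Say also whether those two events count towards overall pregnancy loss.

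The cost is two table cells, one or two sentences and an entry in the version log. No new data are needed and no analysis method changes.
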